## Abstract

**Background:**

“Interstitial lung disease” (ILD) is a broad term encompassing diseases of different backgrounds. “Interstitial pneumonia with autoimmune features” (IPAF) is a recent term that implies the presence of autoimmunity.

**Objective:**

This study aims to determine the characteristics of Polish patients with IPAF, compare them with patients with other interstitial pneumonias, and search for the prognostic and diagnostic biomarkers of IPAF in serum and bronchoalveolar lavage fluid (BALF).

**Methods:**

This multicenter prospective study plans to recruit 240 participants divided into 1 study group and 2 control groups. Biological fluid samples will be collected according to Polish Respiratory Society management guidelines and stored at –80°C for further tests. Prospective 5-year observations of 60 newly diagnosed individuals are planned. The study will be divided into subsections. First, we plan to characterize Polish patients with IPAF (study group) against their peers with other ILDs (2 control groups). Control group 1 will comprise patients with idiopathic ILDs, including mainly idiopathic pulmonary fibrosis and nonspecific interstitial pneumonia. Control group 2 will comprise patients with connective tissue disease–associated interstitial lung diseases, such as rheumatoid arthritis, systemic sclerosis, polymyositis, dermatomyositis, Sjögren’s syndrome, mixed connective tissue disease, and systemic lupus erythematosus. Radiological and functional parameters will be analyzed. Patients will be compared in terms of high-resolution computed tomography results, the 6-minute walking test performance, and pulmonary function test parameters. The diagnosis of IPAF will be reassessed on a regular basis through multidisciplinary discussion in order to determine its clinical stability. In the laboratory arm, inflammation and fibrosis pathways will be assessed. Cytokine levels (interleukin 8, transforming growth factor beta 1, chemokine C-C motif ligand [CXCL]18, CXCL1, surfactant protein [SP]-A, SP-D, Krebs von den Lungen-6 protein, and chitinase 1) will be measured in serum and BALF. A comparative analysis of serum and BALF cytokine levels will be performed in order to establish potential differences between systemic and local inflammatory pathways. In the quality of life (QoL) arm of the study, dyspnea and cough and their impact on various aspects of the QoL will be assessed. Depression and anxiety will be measured with the Hospital Anxiety and Depression Modified Scale and the 9-item Patient Health Questionnaire, and potential correlations with symptom prevalence will be assessed.

**Results:**

This study will start recruiting patients to phase 1 in October 2023. The final results will be available in 2028. We plan to publish preliminary results after 2-3 years from the start of phase 1.

**Conclusions:**

This study will be a step toward a better understanding of IPAF etiopathogenesis and outcomes.

**International Registered Report Identifier (IRRID):**

PRR1-10.2196/44802

## Introduction

### Background

Interstitial pneumonia with autoimmune features (IPAF) was defined in 2015 by the Working Group of the European Respiratory Society (ERS) and the American Thoracic Society (ATS) as interstitial pneumonia with some clinical or serological or both types of features suggesting the presence of an underlying autoimmune disorder. However, no diagnostic criteria for any autoimmune disease are met in these patients during thorough rheumatological workup [1].

“Interstitial lung disease” (ILD) is a broad term encompassing a varied group of disorders. This includes idiopathic interstitial pneumonias (IIPs) and ILDs stemming from environmental exposure or occurring during the course of systemic diseases [2,3].

Data regarding the etiopathogenesis and natural course of IPAF are still lacking. As this is a diagnosis at the crossroads of pulmonology and rheumatology, retrospective and optimally prospective observational studies may cast more light on this subject. Retrospective studies suggest that survival in IPAF does not substantially differ from that in connective tissue disease–associated interstitial lung disease (CTD-ILD) or idiopathic pulmonary fibrosis (IPF), and prospectively, merely 10% of patients with IPAF are reclassified as having CTD-ILD, mostly on the myositis spectrum [4].

Another clinical challenge is in establishing a subset of clinical traits associated with the development of progressive interstitial fibrosis and the loss of lung function. Another retrospective study [5] on individuals with IPAF and CTD-ILD revealed that yearly decline in the forced vital capacity (FVC) is significantly more pronounced in IPAF than in CTD-ILD. Progression is influenced by the presence of anti–Sjögren’s syndrome–related antigen A (anti-SSA) antibodies and postexercise pulse increase in the 6-minute walking test (6MWT) [5].

Most available analyses of the ILD-related quality of life (QoL) and the influence of respiratory and psychological symptoms focus on the most prevalent entities (eg, IPF or sarcoidosis). Research on QoL evaluation in IPAF and its comparison with other ILDs is still scarce. Individuals with chronic disease often present with multiple symptoms, which results in decreased functioning and high medical and societal costs [6]. Depression and anxiety also contribute to the burden of chronic disease.

### Objectives

The primary purpose of this study is to determine the incidence of IPAF in comparison with IIPs and ILDs occurring during the course of autoimmune diseases in 6 Polish pulmonological centers. Further objectives of this study include determination of the clinical, serological, functional, radiological, and histopathological characteristics of patients with IPAF; analysis of diagnostic strategies for specific IPAF subgroups; determination of the potential diagnostic, predictive, and prognostic features of IPAF; and prospective 5-year assessment of patients with IPAF in order to determine the stability of the diagnosis and potential progression to other diseases (eg, CTDs). Please see Figure 1 for the study protocol. To the best of our knowledge, this is the first prospective study focused on patients with IPAF, CTD-ILD, and IIP in Eastern Europe.

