### Study Design

#### Phase 1

All patients meeting the inclusion criteria and not meeting the exclusion criteria regardless of prior treatment history will be recruited to phase 1 of the study. The recruitment process duration is estimated at 12 months. The previous recruitment of 40 patients led to a pilot study [7], which impacted further study design. The maximum number of patients included in this phase will be 80 (33.3%) in the IPAF group, 80 (33.3%) in the CTD-ILD group, and 80 (33.3%) in the IIP group.

#### Phase 2

Only patients with newly diagnosed disease (eg, no prior diagnosis of ILD and, hence, no prior treatment) will be recruited. The estimated recruitment duration is 36 months. The number of patients to be included in this phase will be 20 (33.3%) in the IPAF group, 20 (33.3%) in the CTD-ILD group (only those with RA, SSc, PM/DM), and 20 (33.3%) in the IIP group (only those with IPF, NSIP, COP, LIP; optimally 10, 50%, patients in the IPF subgroup and 10, 50%, in the non-IPF subgroup). Patients who were previously recruited to phase 1 of the study and meet the inclusion criteria of phase 2 may also be included.

Please see Figure 2 for a flowchart of the study design.

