### Impact of Pilot Study Results on the Protocol

In our pilot study [7], we revealed a greater prevalence of gastrointestinal reflux disease (GERD) in the CTD-ILD group than in the IPAF and IIP groups. Data on the impact of GERD on fibrosis pathogenesis are conflicting. There are data suggesting that exposure of the interstitial tissue to a low pH results in repeated lesions and, consequently, progressive fibrosis. However, there are also data supporting a hypothesis that GERD actually results from progressive fibrosis and a shift in intrathoracic pressure due to altered anatomy. Therefore, we decided to launch a substudy on patients with progressive fibrosing ILD (PF-ILD), focusing on the impact of GERD on the disease course. We will monitor 24-hour impedance-pH to objectify GERD episodes and correlate them with symptoms.

In the pilot study [7], it was also revealed that BALF levels of interleukin 8 (IL-8), CXCL1, and TGF-β1 were significantly higher in the CTD-ILD group than in the IPAF and IIP groups. We hope that the analysis of 240 subjects in this full-size study will reveal more defined differences between study groups. We plan to analyze subgroups (eg, RA-ILD or SSc-ILD) and compare them with their IPAF counterparts (based on the presence of clinical symptoms and specific autoantibodies). We also plan to distinguish an IPAF subgroup associated with the presence of antisynthetase autoantibodies and compare it with the PM/DM-ILD subgroup in terms of clinical stability and outcomes.

Our pilot study [7] also revealed that the BALF IL-8 concentration is associated with the presence of skin teleangiectasias. IL-8 is a known proangiogenic factor. In this full-size study, we plan to perform videocapillaroscopy to stratify participants according to the Cutolo nailfold capillaroscopy classification and measure the concentration of proangiogenic cytokines in both serum and BALF. We will be able to compare corresponding Cutolo subgroups of SSc-ILD and IPAF and determine the impact of proangiogenic factors on pathological angiogenesis.

We also hypothesize that there will be significant intergroup differences between the reported severity of cough and dyspnea as well as psychological symptoms and their impact on various aspects of the QoL.

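### The primary purpose is the incidence of IPAF relative to IIP and CTD-ILD, but recruitment to equal per-diagnosis caps means the enrolled counts cannot answer it if the planned totals are reached

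*Protocol article*

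**What the plan says.** The Objectives section puts one aim first: "The primary purpose of this study is to determine the incidence of IPAF in comparison with IIPs and ILDs". The ILDs meant are those of autoimmune disease, and the setting is six centers. Clinical characterization, diagnostic and prognostic features, and five-year stability of the diagnosis are listed there as further objectives.

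The abstract leads with a different aim: "This study aims to determine the characteristics of Polish patients with IPAF, compare them with patients with other interstitial pneumonias". It adds a biomarker search and does not mention incidence.

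Sampling is by diagnosis.

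- Phase 1 (Study Design): "The maximum number of patients included in this phase will be 80 (33.3%) in the IPAF group". The CTD-ILD and IIP groups have the same ceiling. On timing: "The recruitment process duration is estimated at 12 months". Patients enter whatever their treatment history, provided they meet the inclusion criteria and none of the exclusion criteria.
- Phase 2 (Study Design): "The number of patients to be included in this phase will be 20 (33.3%) in the IPAF group". Each of the other two groups also has 20. Only newly diagnosed patients enter, and the CTD-ILD and IIP groups are limited to named subtypes.

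The planned total is stated in the abstract: "This multicenter prospective study plans to recruit 240 participants divided into 1 study group and 2 control groups". The section on the pilot study's impact relies on the same total: "We hope that the analysis of 240 subjects in this full-size study will reveal more defined differences between study groups".

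**The concern.** Relative frequency is a property of the stream of patients arriving at the centers. Once patients are taken by diagnosis up to equal limits, the ratio of the groups in the cohort is set by the limits and no longer by that stream. The study then samples on the very quantity its primary purpose asks about.

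The risk is that a relative incidence computed from participants would simply report the recruitment caps. No later analysis of the enrolled counts can recover the lost information, so this has to be settled in the objective or in what is recorded during recruitment. The other aims (characterization, biomarkers, follow-up) do not depend on incidence and are unaffected.

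**Working it through.** **Inputs.** From Study Design: phase 1 maximum 80 per group; phase 2 number 20 per group; three groups. From the abstract and the pilot-impact section: 240 planned. From the abstract and Visit 2: 60 newly diagnosed patients followed. The article gives no case mix and no center volumes, so those used in step 3 are assumptions.

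**1. Reproducing the plan's figures.** 3 × 80 = 240 and 3 × 20 = 60. The shares are 80/240 = 20/60 = 33.3%. All agree with the article. The total of 240 can be reached only if all three phase 1 groups fill.

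**2. At the planned totals.** IPAF:CTD-ILD:IIP is 80:80:80 and 20:20:20, so every ratio is 1.0 and the IPAF share is 33.3%. This needs no assumption about the true frequencies.

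**3. Short of the planned totals.** Phase 1 gives a ceiling, so partial filling was examined. With N eligible patients and true share p for a group, the enrolled number is approximately min(80, N × p). Worked example, assumed mix IPAF/CTD-ILD/IIP = 10/30/60% and N = 480: expected 48, 144 and 288; after the caps 48, 80 and 80; IPAF share 48/208 = 23.1%. A simulation with Poisson counts cut off at 80 (20,000 replicates) gave:

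| Assumed mix (%) | Eligible N | Mean enrolled (IPAF / CTD-ILD / IIP) | Enrolled IPAF share | True share |
|---|---|---|---|---|
| 10/30/60 | 120 | 12.0 / 36.0 / 71.2 | 10.1% | 10% |
| 10/30/60 | 240 | 24.0 / 71.1 / 80.0 | 13.7% | 10% |
| 10/30/60 | 480 | 48.0 / 80.0 / 80.0 | 23.0% | 10% |
| 10/30/60 | 800 | 76.5 / 80.0 / 80.0 | 32.3% | 10% |
| 10/30/60 | 1500 | 80.0 / 80.0 / 80.0 | 33.3% | 10% |
| 20/30/50 | 120 | 24.0 / 35.9 / 59.8 | 20.0% | 20% |
| 20/30/50 | 240 | 47.9 / 71.2 / 80.0 | 24.0% | 20% |
| 20/30/50 | 480 | 79.8 / 80.0 / 80.0 | 33.3% | 20% |

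The enrolled share is close to the truth only in the rows with about 120 enrolled, half the planned 240. As enrollment approaches the target, the share moves to one third.

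**4. Patients needed to fill the IPAF group.** To expect 80 IPAF patients, 80/p eligible patients are needed: 80/0.10 = 800, 80/0.15 = 534 (rounded up), 80/0.20 = 400, 80/(1/3) = 240. At any true IPAF share below one third, at least one other group must be cut off at its cap before the IPAF group fills. If the three diagnoses really were equally common, the enrolled share would be right, but the data could not distinguish that case from the others.

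**5. New versus existing cases.** Phase 2 requires a new diagnosis. Phase 1 has no such requirement, so its counts need not be counts of new cases even before the caps act. Phase 2 is restricted to new cases, but its group sizes are set and its subtypes are restricted.

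**The case against.** Several points on the other side are fair.

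- **The 80 is a ceiling.** A reader might infer that phase 1 sizes are fixed and that the IPAF share is one third by construction. The wording does not support that: "The maximum number of patients included in this phase will be 80 (33.3%) in the IPAF group" sets a maximum, and only phase 2 states a set number. The Results section reports past recruitment difficulty, so underfilling is possible. This stands. The conclusion is therefore conditional on reaching 240, which is nevertheless what the article plans for.
- **Other data could supply the frequency.** A reader might infer that the study cannot estimate it at all. A consecutive-case log, or the time each group takes to fill, could help. The article describes neither, but the full protocol might, and the two study diagrams are not reproduced. Phase 1 also speaks of recruiting all eligible patients, although the caps limit that. What is supported is the narrower statement about enrolled counts.
- **The statistical section names no proportion or rate.** That is commonly left to an analysis plan, which is not shown. It is not part of this point.
- **Prevalent cases.** A reader might infer that phase 1 certainly mixes treated, prevalent patients with new ones. Study Population excludes a history of ILD therapy, and phase 1 itself requires that no exclusion criterion be met, so the documents conflict on treatment. Earlier treatment is also not the same as earlier diagnosis. What stands is that phase 1 does not require a new diagnosis and that the two statements must be reconciled.
- **The size of any overstatement.** A multiplier needs a true IPAF share, which the article does not give. The mixes in the table only illustrate the mechanism.

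**Conclusion.** The concern holds in conditional form. The stated primary purpose and the stated recruitment do not fit together: if the planned 240 and 60 are reached, the enrolled IPAF share is 33.3% and all group ratios are 1.0 regardless of the truth. That result rests only on the article's own numbers. The statement that enrolled counts approach the truth only when the phase 1 caps rarely bind, well short of 240, rests on the assumed mixes and volumes for its figures but not for its direction, provided the true mix is not equal thirds. The documents do not show that phase 1 sizes are fixed, that no other source of frequency data exists, or how far a reported frequency would be from the truth.

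**What to change.** **Preferred.** Make the abstract's aim the primary objective: characterize patients with IPAF and compare them with the two control groups. Drop incidence from the Objectives section. The cost is a wording change, with no effect on recruitment or procedures.

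**Alternative, if a frequency aim is to stay.** Estimate it outside the capped cohort. Over a defined window, each of the six centers counts every consecutive newly diagnosed ILD patient as IPAF, CTD-ILD, IIP or other, with no cap. Report the share with an exact 95% CI, overall and by center, and call it relative frequency among referred patients, because there is no population denominator. The count must start with recruitment, since patients turned away after a group fills would otherwise be lost. For orientation, at an assumed 10% IPAF share the approximate half-width 1.96 × √(0.1 × 0.9/N) is 3.4, 2.6 or 1.9 percentage points for N = 300, 500 or 1000; exact limits will differ slightly.

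The alternative costs a small logging burden. It may also need ethics approval for de-identified counts of people who are not enrolled, because Ethical Considerations describes data collection under signed consent. Non-enrolled patients would have to be classified from the diagnosis reached in routine care.

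**In either case,** reconcile the phase 1 statement on earlier treatment with the exclusion of previous ILD therapy in Study Population, and state whether phase 1 admits patients diagnosed before the study.

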**Figure 1 figure1:**
[figure not shown]
Study protocol. BALF: bronchoalveolar lavage fluid; IIP: idiopathic interstitial pneumonia; IPAF: interstitial pneumonia with autoimmune features.

## Methods

### Study Population

Inclusion criteria are as follows: individuals with ILDs, aged ≥18 years, and able to provide informed consent.

The study group will comprise patients with IPAF defined according to the criteria established by the Working Group of the ERS and the ATS [1]. Control group 1 will comprise patients with the following CTD-ILDs: rheumatoid arthritis (RA), systemic sclerosis (SSc), polymyositis (PM), dermatomyositis (DM), Sjögren’s syndrome (SS), mixed connective tissue disease (MCTD), and systemic lupus erythematosus (SLE) diagnosed according to the diagnostic criteria issued by the European League Against Rheumatism (EULAR) or the American College of Rheumatology (ACR). Control group 2 will comprise patients with the following IIPs: IPF, nonspecific interstitial pneumonia (NSIP), cryptogenic organizing pneumonia (COP), acute interstitial pneumonia (AIP), respiratory bronchiolitis–associated interstitial lung disease (RB-ILD), desquamative interstitial pneumonia (DIP), and lymphocytic interstitial pneumonia (LIP). Previously untreated patients with a new diagnosis of ILD were recruited for a pilot study (a separate population of patients) [7].

Exclusion criteria include age<18 years; respiratory tract infection, including minor upper respiratory tract infections (eg, the common cold) 4 weeks prior to the diagnostic process; asthma; tuberculosis; asbestosis; chronic hypersensitivity pneumonia; Hermansky-Pudlak syndrome; and other causes of genetic ILDs (eg, lymphangioleiomyomatosis, tuberous sclerosis complex [TSC], Birt-Hogg-Dubé syndrome, dyskeratosis congenita, familial forms of ILD, immunodeficiency syndromes); a history of therapy for ILD, including systemic glucocorticosteroids (GCs; both pulsed and long-term low-dose therapy); pregnancy and nursing; malignancy; HIV seropositivity; and a lack of ability to provide informed consent. For the QoL arm of the study, we will also exclude participants unable to communicate verbally.

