Another question is when to initiate treatment during the course of IPAF. Before IPAF was defined, ILD with symptoms of underlying autoimmune disorder but without extrapulmonary manifestation could have been classified as IIP and therefore have delayed treatment initiation. In our prospective observational study, we will surely face a challenge in identifying patients with IPAF who require early clinical intervention. We hope that during the 60-month observation period, we will be able to identify molecular, radiological, and functional prognostic factors, which, in the future, will help lay the foundation for IPAF therapy guidelines.

In a study on 412 patients with CTD-ILD or IPAF, Li et al [56] analyzed the relationship between these 2 entities in order to identify which individuals with IPAF should commence treatment early. They concluded that based on similar yet milder symptoms and ANA positivity, IPAF is in fact an early stage of CTD-ILD and therefore treatment should commence early. After immunosuppressive treatment, they reported an increase in the FVC and DLCO in this population. The choice of adequate pharmacotherapy is another clinical question that we will face during prospective observation.

D’Silva et al [57] presented a case series of 50 patients from 2 centers who were treated with rituximab (RTX). The majority experienced either clinical improvement or stability understood as global assessment of performance in terms of oxygen requirement, unplanned hospitalization due to respiratory reasons, and 1-year survival, despite baseline differences regarding age, comorbidities, and prior treatment history.

Although we do not plan a randomized controlled trial, in prospective observation, we will face clinical decisions regarding treatment implementation. We hypothesize that some patients will have a history of treatment with systemic GCs or cyclophosphamide (CYC), and we wonder whether the results of studies on CTD-ILDs can be extrapolated to the IPAF population. The use of CYC is associated with an increased risk of malignancy, infections, and bone marrow suppression [58].

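### Prior ILD therapy is a study-wide exclusion in one section and is disregarded for phase 1 in another, so who may enter the 240-patient cohort is undefined

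*Protocol article*

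**What the plan says.** Four places in the protocol article bear on prior treatment.

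- **Methods, Study Population.** The exclusion list includes "a history of therapy for ILD, including systemic glucocorticosteroids (GCs; both pulsed and long-term low-dose therapy". It is not tied to a phase. The same paragraph does limit another exclusion, which applies only to the quality-of-life arm.
- **Study Design, Phase 1.** The entry rule is "All patients meeting the inclusion criteria and not meeting the exclusion criteria regardless of prior treatment history will be recruited to phase 1". On size, "The maximum number of patients included in this phase will be 80 (33.3%) in the IPAF group", with the same cap for the CTD-ILD and IIP groups. On time, "The recruitment process duration is estimated at 12 months".
- **Study Design, Phase 2.** The entry rule is "Only patients with newly diagnosed disease (eg, no prior diagnosis of ILD and, hence, no prior treatment) will be recruited". Phase 1 patients who meet the phase 2 criteria may carry over.
- **Discussion, Summary.** "We hypothesize that some patients will have a history of treatment with systemic GCs or cyclophosphamide (CYC".

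The abstract says the study "plans to recruit 240 participants divided into 1 study group and 2 control groups". The Objectives name six centers. The Statistical Analysis section gives ANOVA or Kruskal-Wallis for the three-group comparison, plus correlation and linear regression. It does not mention prior treatment.

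**The concern.** Eligibility has to be readable in one way. Here a previously treated patient is barred by the exclusion list and admitted by the phase 1 sentence, which itself invokes that list. A center following the list would enroll only untreated patients. A center following the end of the phase 1 sentence would also enroll treated ones. No statistical analysis plan can repair this, because it is settled at screening.

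The secondary stake is interpretation. If treated patients enter and treatment is unevenly spread across IPAF, CTD-ILD and IIP, a difference in a serum or BALF marker could partly reflect therapy. The article itself gives a reason to care. The section on candidate biomarkers cites a study in which SP-A differed before and after treatment in patients with IPAF and progressive fibrosis. That study does not isolate a drug effect, since progression is an alternative explanation, but it is enough to make treatment status at sampling worth knowing.

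**Working it through.** **1. Size of the cohort affected.** Inputs are the group sizes under Study Design. Phase 1: 3 × 80 = 240, which matches the total in the abstract. Phase 2: 3 × 20 = 60, which matches the number given under Visit 2. The article states no power calculation, so there is none to reproduce.

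**2. The statements side by side, for a patient already treated for ILD.**

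| Place | Consequence for a treated patient |
|---|---|
| Study Population, exclusion list | Excluded, no phase named |
| Phase 1, first half of the sentence | Excluded, because the exclusion criteria apply |
| Phase 1, second half of the sentence | Admitted, because treatment history is disregarded |
| Phase 2 | Excluded |
| Discussion, Summary | Expected among the patients |

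Two readings can be tried.

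- *The exclusion list governs both phases.* The second half of the phase 1 sentence then has no effect, the absence of earlier treatment no longer separates the phases, and the Discussion remark has little to refer to.
- *Phase 1 waives the therapy exclusion and phase 2 restores it.* The phase descriptions and the Discussion then agree, but the exclusion list is wrong as printed because it lacks a phase qualifier.

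Each reading requires some printed text to be set aside. The article does not say which.

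**3. What can be said about bias if treated patients enter.** For two groups with no true difference, the spurious difference is approximately

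bias = (difference in treated share) × (treatment effect in SD units).

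The article gives neither factor. As an illustration only, assume treated shares of 70% and 20% and an effect of 0.3 to 0.8 SD:

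- (0.70 − 0.20) × 0.3 = 0.15 SD
- (0.70 − 0.20) × 0.8 = 0.40 SD

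With share differences of 20 to 60 points and the same effects, the bias runs from 0.2 × 0.3 = 0.06 SD to 0.6 × 0.8 = 0.48 SD. An unadjusted pairwise comparison with 80 per group at a nominal 5% (normal approximation, standard error √(2/80) = 0.158) would then reject in 6.7% to 85.9% of cases. A range that wide shows only that the answer depends on unknown inputs. It is also a two-group calculation, whereas the plan names a three-group test.

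**4. Precision cost of restricting to untreated patients.** Under the same assumed 70% and 20%, the untreated numbers are 80 × 0.30 = 24 and 80 × 0.80 = 64. The standard error of the contrast becomes √(1/24 + 1/64) = 0.239, against 0.158 with everyone: a ratio of 0.239/0.158 ≈ 1.51, or about 51% larger.

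**The case against.** The best defense is that the specific phase rule qualifies the general list, so phase 1 waives the therapy exclusion and phase 2 reinstates it. That is a coherent reading, and the study flowchart, which was not available here, may say so. It stands as an explanation of what may be meant. It does not make the printed exclusion list correct, and a screening center should not have to infer the waiver. The Discussion remark is also weak support on its own: it is phrased as a hypothesis and sits among questions about treatment decisions during follow-up.

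Two stronger conclusions are tempting.

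*That phase 1 is infeasible if the exclusion governs.* A reader might compare 240/12 = 20 patients per month in phase 1 with 60/36 = 1.67 per month in phase 2, a 12-fold gap, and infer that only treated patients could fill it. The documents do not support this. These are targets divided by recruitment windows, not counts of available patients. The 80 per group is a maximum. Phase 2 takes fewer diagnoses, only new ones, and follows them for five years. Patients already diagnosed but never treated could enter phase 1 under either reading.

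*That the marker comparisons are confounded.* This needs treatment to differ between groups and to move the markers. The article states no treatment frequencies by diagnosis. A statistical analysis plan that is not shown may adjust for treatment, and the linear regression named in the article leaves room for it. The medical history at Visit 1 may already capture past therapy. Confounding is therefore a risk that depends on how the contradiction is settled.

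**Conclusion.** The contradiction is on the face of the document and holds with high confidence. The exclusion list and the phase 1 sentence cannot both be followed for a previously treated patient, and no visible text reconciles them. It determines eligibility for the whole phase 1 cohort, up to 240 patients at six centers, so it must be fixed. This conclusion rests on no numerical assumption.

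The effect on marker comparisons is conditional. It arises only if treated patients may enter, and its size cannot be derived from the article; the bias and rejection figures above are illustrations on assumed inputs. Infeasibility of phase 1 is not established.

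**What to change.** **Required.** Reconcile the Study Population and Study Design sections by stating, in the exclusion criterion itself, which phase or phases the prior-therapy exclusion covers, and align the Discussion with it. Which rule to adopt is for the sponsor. The cost is the wording of one criterion, communicated to all six centers.

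**If treated patients may enter phase 1.**

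- Record treatment status at each serum and BALF sampling, with drug class and time since last dose, unless the Visit 1 questionnaire already does so.
- Keep the planned ANOVA or Kruskal-Wallis comparison and add two analyses beside it: one adjusted for treatment status, and one sensitivity comparison limited to patients untreated at sampling.

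This costs a few data fields and some extra analysis. The untreated subset will be less precise, by about 51% in standard error under the assumed 70% and 20% split, which is why it is proposed as a sensitivity analysis and not as the primary population.
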